## Abstract

**Background:**

Approximately 85% of women experience an obstetric tear at delivery and up to 25% subsequently experience wound dehiscence and/or infection. Previous publications suggest that intravenous antibiotics administrated during delivery reduces this risk. We do not know if oral antibiotics given after delivery can reduce the risk of wound dehiscence or infection. Our aim is to investigate whether three doses of oral antibiotics (amoxicillin 500 mg/clavulanic acid 125 mg) given after delivery can reduce the risk of wound dehiscence and infection in patients with a second-degree obstetric tear or episiotomy.

**Methods:**

We will perform a randomized, controlled, double-blinded study including 221women in each arm with allocation 1:1 in relation to the randomization. The study is carried out at Department of Obstetrics & Gynecology, Herlev University Hospital, Copenhagen, Denmark. The women will be included after delivery if they have had a second-degree tear or episiotomy. After inclusion, the women will have a clinical follow-up visit after 1 week. The tear and healing will be evaluated regarding signs of infection and/or dehiscence. The women will again be invited for a 1-year clinical examination including ultrasound. Questionnaires exploring symptoms related to the obstetric tear and possible complications will be answered at both visits. Our primary outcome is wound dehiscence and/or wound infection, which will be calculated using *χ*^2^ tests to compare groups. Secondary outcomes are variables that relate to wound healing, as pain, use of painkillers and antibiotics, need for further follow-up, as well as outcomes that may be related to the birth or healing process, urinary or anal incontinence, symptoms of prolapse, female body image, and sexual problems.

**Discussion:**

Reducing the risk of wound dehiscence and/or infection would decrease the number of control visits, prevent the need for longer antibiotic treatment, and possibly also decrease both short-term and long-term symptoms. This would be of great importance so the mother, her partner, and the baby could establish and optimize their initial family relation.

**Trial registration:**

The conduction of this study is approved the 2/2–2023 with the EU-CT number: 2022–501930-49–00. ClinicalTrials.gov Identifier: NCT05830162.

**Supplementary Information:**

The online version contains supplementary material available at 10.1186/s13063-024-08069-x.

## Background

Approximately 85% of women experience an obstetric tear at delivery [1, 2]. A second-degree tear is the most common type, and it involves the skin, vagina, and the underling muscles of the pelvic floor. Up to 25% of women with this form of tear subsequently develop wound infection or dehiscence [1, 3]. Wound infection, defined as abscess formation or secretion of pus from the rupture [4], can cause painful and reduced healing and wound dehiscence as well as long-term consequences, for example dyspareunia and weakening of the pelvic floor. Wound dehiscence is defined as diastasis of more than 5 mm between the wound edges and is seen in up to 25% in women with a second-degree tear or an episiotomy [1, 3].

A recent large randomized controlled study found that intravenously administered antibiotics during instrumental delivery could reduce the risk of maternal infections in the maternity period [5]. In the study, the authors found as an incidental finding that women receiving antibiotics had a 50% reduced risk of obstetric tear wound dehiscence and infection. Another study also reported a lower prevalence of wound dehiscence and infection in the group of women that received antibiotic treatment during delivery, although the association between antibiotics and risk of complications after obstetric tear was not their primary outcome [3]. In Denmark, it is not the standard treatment to prescribe antibiotics to women with a second-degree tear or an episiotomy. We therefore want to investigate if orally administrated antibiotics within the first day after suture of a second-degree perineal tear or an episiotomy reduces the risk of wound dehiscence or infection.

## Methods

The REPAIR study is a randomized, placebo-controlled, double-blinded trial investigating the effect of prophylactic antibiotic to women with a second-degree obstetric tear or episiotomy on risk of infection and/or wound dehiscence. The study will include 221 women in each arm with allocation 1:1 in relation to the randomization. The study is carried out at the Department of Obstetrics & Gynecology, Herlev University Hospital, Copenhagen, Denmark. We used the SPIRIT reporting guidelines in the protocol [6], and checklists are submitted (see Additional file 1). For additional trial registration information and expected timeline of this study, see Figs. 1 and 2.

**Fig. 1 Fig1:**
[figure not shown]
WHO trial registration data set

**Fig. 2 Fig2:**
[figure not shown]
SPIRIT figure

## Study set up

### Information about the project

Participants should start the preventive treatment with antibiotics shortly after birth to have the intended effect, and therefore, the usual reflection time of 24 h cannot be given in this study. To optimize the decision process and support the women in making a well-informed confirmed consent, information about the project will be available in the antenatal period. Pregnant women at Herlev Hospital will receive information by digital post, by posters in the departments, as well as during birth preparation classes where the primary investigators will be present to give information and answer questions. Further contact information will be available for the women to use if they have any questions concerning the study. Thus, the women should be better prepared to give informed consent within a few hours after delivery.

The Danish monitor “Good Clinical Practice unit” (GCP) will monitor and approve the study before beginning of inclusion and during the entire study period.

### Screening

Physicians attending the labor ward are specially trained in the inclusion process. The primary investigators are responsible for this training. Physicians are hereafter responsible for screening all women with a second-degree tear or episiotomy for potential enrollment in the study based on the following inclusion and exclusion criteria.

Inclusion criteria.Liable Danish-speaking women > 18 years of ageSecond degree perineal tear and/or episiotomySuturing of obstetric tear at Herlev Hospital

Exclusion criteria.Allergies to the treatmentWomen who end up with a cesarean-section, including those who have obstetric tears that require stitching or have had an episiotomyWomen who receive antibiotics intra- or postpartum for other reasons

### Inclusion

Each potential candidate for inclusion in the study will be informed about the purpose and content of the project by a medical doctor in accordance with the recommendations of the Scientific Ethics Committee. The information covers the possible advantages and disadvantages and will be easy understandable. If a woman wants to participate in the trial, the consent form is signed.

All included women are informed that they can withdraw their consent to participate in the project at any time and without reason, without affecting current or later treatment. They are also given the leaflet “Your rights as a subject in a biomedical research project from the Central Scientific Ethics Committee.”

After inclusion, the physician including a woman in the study is responsible for handling the project medicine to her.

### Intervention

Placebo and amoxicillin 500 mg/clavulanic acid 125 mg will be obtained from The Capital Region Pharmacy, who will be responsible for the randomization process. The randomization will occur during the packing chronological ID-number medicine boxes each containing either placebo or the intervention medication. By establishing the randomization prior to enrollment, we avoid selection bias at the inclusion process. The medication will be stored in a locked medicine room at the maternity ward. The principial investigators will be responsible for control and handling of the trial medicine.

At inclusion, the women will be given the next chronological ID-number corresponding to a medicine box. The participant is then randomized to have either amoxicillin 500 mg/clavulanic acid 125 mg or placebo medicine for 1 day after delivery (three doses in total administrated with 8-h intervals). The blinding will be kept for both the participants, the including doctor, the principal investigators, and all four authors of this paper until the last visit for the last patient.

The randomization will be an individual level randomization with an allocation ratio of 1:1 to amoxicillin 500 mg/clavulanic acid 125 mg or placebo. Randomization will occur in blocks to reduce the risk of unblinding. The randomization process will not be stratified. The randomization will be based on a computer-generated random-number allocation sequence stored at the pharmacy. The randomization sequence will not be available to staff involved in data management, analysis, report writing, or patient care until breaking of the randomization code.

### Side effects and risks

Women are informed at inclusion about the medication, including possible side effects. The combination of amoxicillin and clavulanic acid is well-known and approved treatment and are given in a standard dose in a very short interval (three tablets over 24 h). The antibiotic can be used during breastfeeding [7], and given the combination of a short-term dosage before the milk production has started, we expect minimal side effects on the infants.

Side effects for the mother are also expected to be small due to the low dose and short-term treatment period. The assessment if a woman has experienced side effects to the medicine will be evaluated at the initial consultation after delivery. This cut off point for evaluation of side effect was chosen because amoxicillin with clavulanic acid has a half-life of 1 h, and it can therefore be expected that any side effects would have occurred at the first control visit 7–10 days after administration of the medicine. If the participant experience acute side effects after the first pill, she is informed not to continue the treatment but will still be able to continue for follow-up if desired. If a patient experience serious side effect and the doctor treating the patient wish to know if the participant had antibiotics, unblinding for that participant can be done. This unblinding will be handled by the investigator or sponsor by opening the code curve for that patient. The CGP-monitor will be informed about that directly hereafter.

### Initial consultation

The initial clinical consultation in the trial is scheduled 7–10 days after the delivery, with accepted intervals between 4 and 14 days after inclusion. The timepoint will be noted in the file to enable adjustment for this in the final analysis. In case of clinical symptoms before the initial consultation, the women are given detailed instructions to contact the Obstetric Department on a 24-h telephone line, thereby providing standard care.

At the initial consultation, the participant is asked to fill in a questionnaire regarding pain, urinary incontinence, and anal incontinence. Furthermore, she will be asked if she has been prescribed antibiotics for other reason since delivery, if she took all three doses of the study medication (compliance), and if she suffered from any medical side effects. All potential side effects will be evaluated by the physician performing the clinical examination. The tear will be examined by physicians specially trained for the study. In case of doubt about wound dehiscence or infection, other physicians will examine the participant to reach consensus.

In case of cancelation of the initial consultation, the participants will receive a personal phone call to clarify if she is willing to fill in the questionnaire and if she wants to be contacted for the 1-year clinical examination.

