## Discussion

This randomized controlled double-blinded study evaluates whether oral antibiotics can prevent wound dehiscence or infection after second degree obstetric tears or episiotomy compared to placebo. The study has the possible advantage for the group receiving antibiotics that they might have a lower risk of infection and wound dehiscence compared to the control group. Conversely, this group also has a risk of side effects to the medication. The antibiotic used in this study is a frequently used medication that can also be used in breastfeeding women [7]. The placebo group will most likely not experience any side effects but conversely do not have the possible protective effect with respect to risk of infection or wound dehiscence. It is not standard in Denmark to treat second-degree tear or episiotomy with antibiotics and therefore the placebo group in this study is treated in accordance with national guidelines. Both groups are offered consultation with a physician in the first 2 weeks as well as 9–12 months after birth, which is not offered routinely today. This may be of concern to some of the women who will think more about the tear and recovery than they otherwise would have done. However, it can also have a calming effect on some of the trial participants that the tear and healing is being monitored and that it is assessed by a health care professional. For participants experiencing infection and/or wound dehiscence, the initial consultation can result in earlier diagnosis and treatment and, thus, potentially improved outcome. Conversely, some women might have tendency to postpone contact with their own general practitioner for a check-up, because they are waiting for the scheduled appointment in study. However, the participants are thoroughly informed about the importance of contacting a physician if they experience any discomfort before the initial consultation.

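### The physician who grades the wound also evaluates side effects at the same visit, and nothing puts the grading first: a small, cheaply removed risk of functional unblinding

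*Protocol article*

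**What the plan says.** The initial consultation yields the primary outcome, wound dehiscence and/or infection. Under Initial consultation, "The tear will be examined by physicians specially trained for the study". The woman is asked about other antibiotics, whether she took all three doses, "and if she suffered from any medical side effects". The article does not say who asks. It does say who judges the answers: "All potential side effects will be evaluated by the physician performing the clinical examination". Side effects and risks confirms the timing: "The assessment if a woman has experienced side effects to the medicine will be evaluated at the initial consultation after delivery".

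The outcome has physical criteria. In the Background, "Wound dehiscence is defined as diastasis of more than 5 mm between the wound edges", and infection means an abscess or pus. Some judgement remains, because Initial consultation provides for unclear cases: "In case of doubt about wound dehiscence or infection, other physicians will examine the participant to reach consensus".

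On side effects, the Discussion says the antibiotic group carries a risk of them, and then: "The placebo group will most likely not experience any side effects". Side effects and risks expects them to be small, given the low dose and short course.

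On blinding, the Intervention section says: "The blinding will be kept for both the participants, the including doctor, the principal investigators, and all four authors of this paper". It also withholds the randomization sequence from staff involved in patient care.

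**The concern.** Placebo and a concealed sequence keep the allocation from being read directly. They do not stop an examiner from guessing it from what the woman reports. By the article's own expectation, a side effect points to the antibiotic, and the person told to evaluate that side effect is the person who grades the wound. Stopping the tablets early because of an acute reaction, which the article allows for, would give the same clue through the question on doses taken.

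An examiner who suspects antibiotic may be slower to call a gap of about 5 mm a dehiscence, or to call in colleagues. Side effects should be commoner on antibiotic, so missed events would gather in that arm and flatter the treatment. Blinding is the main protection for a clinician-graded primary outcome, so even a small leak is worth closing if that costs little.

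**Working it through.** **Reproducing the plan's figure.** Sample size calculation gives 20% v 10%, significance level 0.05 (taken as two-sided), power 80% and dropout 10%. With pooled variance under the null and no continuity correction:

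n = [1.96 × √(2 × 0.15 × 0.85) + 0.8416 × √(0.20 × 0.80 + 0.10 × 0.90)]² / 0.10² = 198.96, so 199 per arm.

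199 / 0.90 = 221.1, which agrees with the stated 221. The point leaves the sample size unchanged. The checks below use 199 examined women per arm, where power is 80.0%.

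**How strong is the clue?** The article gives no side-effect rates, so these are assumptions: a on antibiotic and b on placebo, as (10%, 3%), (15%, 5%) and (20%, 10%). With 1:1 allocation, the probability that a woman reporting a side effect is on antibiotic is a/(a+b) = 77%, 75% and 67%, against 50% by chance.

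**How far could the result move?** Let m be the fraction of true events missed among women who report side effects. The examiner cannot tell true from false clues, so m applies in both arms:

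- recorded rate on placebo: P = p₁(1 − b·m)
- recorded rate on antibiotic: A = p₂(1 − a·m)
- chance of significance: 1 − Φ((c − d)/s) + Φ((−c − d)/s), where d = P − A, c = 1.96 × √(2p̄(1 − p̄)/199), p̄ = (P + A)/2 and s = √([P(1 − P) + A(1 − A)]/199)

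Worked example: no true effect, 15% in both arms, (a, b) = (15%, 5%), m = 0.5.

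- P = 0.15 × 0.975 = 0.14625; A = 0.15 × 0.925 = 0.13875; d = 0.0075
- c = 0.0687; s = 0.0350
- chance of significance = 0.0404 + 0.0148 = 5.5%

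| a, b | m | Spurious difference, no effect (15% both) | False-positive rate | Recorded difference at 20% v 10% | Apparent power |
|---|---|---|---|---|---|
| 10%, 3% | 0.25 | 0.26 points | 5.1% | 10.10 points | 81% |
| 10%, 3% | 0.50 | 0.53 points | 5.3% | 10.20 points | 82% |
| 15%, 5% | 0.25 | 0.38 points | 5.1% | 10.13 points | 82% |
| 15%, 5% | 0.50 | 0.75 points | 5.5% | 10.25 points | 83% |
| 20%, 10% | 0.25 | 0.38 points | 5.1% | 10.00 points | 81% |
| 20%, 10% | 0.50 | 0.75 points | 5.5% | 10.00 points | 82% |

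In the last two rows the absolute difference stays at 10 points. Power still rises, because both recorded rates fall and the variance with them.

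**Sensitivity to the assumptions.**

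- Widest gap, 20% v 3%, same m: false-positive rate 5.4-6.5%, apparent power 83-86%.
- No gap, 10% v 10%: false-positive rate stays at 5.0% and power falls to 78-79%. Misgrading does no net favour to the antibiotic unless side effects differ by arm.
- No side effects on placebo, 20% events in both arms: 5% reporting with m = 0.25 gives a spurious 0.25 points and 5.0%; 10% with m = 0.5 gives 1.0 point and 5.7%; 20% with m = 0.5 gives 2.0 points and 8.0%.

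**The case against.** The strongest objection is that the article does not fix the order of the visit. The questions come before the examination in the prose, but nothing there says before or after, and no asker is named. Side effects could be evaluated once the wound has been graded, and the order of items on a visit form is detail that an article may leave to the full protocol. This stands as far as it goes: it cannot be said that the examiner already knows the history when grading. What remains is a stated assignment of both tasks to one physician, with no stated separation between them.

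The safeguards also count: placebo, a sequence withheld from care staff, physical criteria, trained examiners and a consensus step. They limit the room for error. A concealed sequence does not prevent guessing, however, and consensus starts only when someone is in doubt, which is itself a judgement open to the clue. The expectation of small side effects over a course of three tablets also stands, and it supports the lower end of the range.

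Two stronger readings are tempting. A reader might infer that the wound examiners are unblinded, because the list of blinded persons does not name them. Withholding the sequence from patient-care staff would cover them, so formal blinding is intact. A reader might also suppose that clues remove 1-2 points of events from the antibiotic arm alone, which gives 88-93% power at 20% v 10% and 6-9% false positives at 15% in both arms. At a 10% event rate, 10-20% of women reporting side effects hold only 1-2 points of events (10% × 10% to 20% × 10%). Every one would have to be regraded, with none on placebo. Even with every such event missed in both arms, the three assumed pairs give 85-86% and 6.1-7.3%.

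**Conclusion.** The point holds as a possible and small risk of functional unblinding of a partly judgement-based primary outcome. The assignment of both tasks to one physician is in the text, and the article itself expects side effects to differ by arm. Nothing shows that grading was in fact influenced.

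Under the three assumed pairs of reporting rates, with 25-50% of the affected women's events missed in both arms, the false-positive rate is about 5.1-5.5% instead of 5% and apparent power about 81-83% instead of 80%. The spurious difference under no effect is 0.3-0.75 points, against a planned 10. Larger values need a wider gap in reporting or heavier misgrading than these assumptions. All reporting and misgrading rates are assumptions. This is a cheap improvement, not a threat to the trial's main result.

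**What to change.** State under Initial consultation that dehiscence, infection and any request for a consensus examination are entered in REDCap before side effects and dose-taking are asked about or evaluated. Answers on those items should not be seen by the examiner before that entry. State also that physicians called in for consensus are not told that history. The same physician can still do both tasks.

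The cost is a re-ordered visit form and a line in the physician training, with no extra staff or participants. One downside is that side effects are discussed at the end of the visit. The other is that visits already held cannot be changed: recruitment began in March 2023 and was expected to finish in spring 2024. For those visits, the trial report should say which order was used and, where side effects came first, name this as a limitation.

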### One-year follow-up consultation

At the 1-year consultation, the participant fills in questionnaires about urinary incontinence, anal incontinence, prolapse problems, body image, breastfeeding, and sexual problems. At this visit, a gynecological and ultrasound examination will be carried out to assess the gynecological anatomical outcome after the birth and obstetric tear. We will evaluate the perineum, the pelvic floor muscles, the anal sphincter, and signs of genital prolapse. Ultrasound will be used to evaluate clinically undiagnosed obstetric anal sphincter injuries, possible defects of the perineal muscles, and damage to the levator ani.

### Outcome

The primary outcome of the trial is the difference in frequency of wound dehiscence and infection in the two groups at 7 to 10 days after delivery. Secondary outcomes are pain, use of painkillers and antibiotics prescribed post-partum, or the need for further follow-up. This information will be extracted from the questionnaire at the initial consultation. Other secondary outcomes are urinary or anal incontinence, symptoms of prolapse, female body image, and sexual problems. These long-term outcomes will be extracted from the questionnaire and the clinical examination at the 1-year consultation. The ultrasonically assessed substance of the perineal muscles, the levator ani muscle, and the anal sphincter are additional secondary outcomes.

